### Eligibility criteria

Inclusion criteria are the followings: 1. diagnosis of AN according to the Diagnostic and Statistical Manual of Mental Disorders, Fifth Edition—DSM-5 (American Psychiatric Association & American Psychiatric Association, 2013), confirmed by experienced developmental psychiatrists and psychologists through extensive clinical examination; 2. a condition of under-weight (BMI < 18.5 kg/m^2^); 3. intelligence quotient (IQ) higher or equal to 85 (IQ ≥ 85); 4. age ranging from 10 to 18 years included; 5. ability to give informed consent under parents' surveillance and guidance.

Exclusion criteria include: 1. a personal history of neurological/medical/genetic diseases; 2. a personal history of epilepsy; 3. suicide risk; 4. receiving CNS-active drug, other counseling or psychological therapies during the treatment.

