#### Physiological measures

Endogenous stress response system functioning and nutritional status will be collected at T0 and T1, as well as T2 and T4, while BMI will be assessed at each evaluation.

To investigate the endogenous stress response system functioning, the HPA axis functioning will be evaluated through the measurement of the Cortisol awakening response (CAR). To this purpose, participants will be instructed to collect saliva samples at home in two consecutive working days. They will be invited to collect saliva samples at awakening (in bed) and 15-, 30- and 60-min following awakening, by using the sampling device “Salivette” (Sarstedt; Rommelsdorft, Germany). Saliva cortisol concentrations will be measured by an enzyme immunoassay method, using a commercially available ELISA kit (Biochem Immunosystem, Milan, Italy). As measures of the CAR, the cortisol area under the curve relative to the ground (AUCg) and the AUC with respect to the increase (AUCi) will be also calculated.

The nutritional state will be evaluated by blood tests: Electrolytes, full blood count, Hematocrit, MCV, folate, B12, TIBC, albumin, transferrin, ESR, protein electrophoresis, serum total cholesterol, high density lipoproteins, triglycerides, glucose profile, glycaemia, insulin, AST, ALT, GGT, FT4, TSH, sexual hormones, cortisol, immunologic evaluation, copper.

Finally, BMI will be calculated as the person’s weight in kilograms divided by the square of height in meters.

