#### Secondary outcome measures

Secondary psychological outcome measures will be collected at T1, T2, T3, T4 and T5, physiological outcome will be collected at T1, T2 and T4 and only BMI also at T3 and T5, instead neurophysiological outcome measures will be collected only at T1.

Improvement on the other EDI-3 composite scores, EAT-26 total score, BUT-GSI, and CBCL 6–18, YSR 11–18, MASC-2 and CDI-2 subscale’s t-scores, will be considered as secondary psychological end-points.

Possible reduction of left and right hemisphere baseline differences in TEPs, in SICI/ICF and SAI protocols, and increase MEP amplitude in iTBS protocol will be considered as neurophysiological secondary end-points.

Finally, reduction in the CAR, CAR AUCg and AUCi and improvement in nutritional state and BMI, which have normative data for age and sex, will be adopted as secondary physiological end-points.

See Table 1 for details on the outcome measures.

**Table 1. Tab1:** Outcome measures.

Primary outcome measure	Secondary outcome measures	
EDRC score (EDI-3)	Psychopatological	IC, IPC, APC, OC, GPMC scores (EDI-3) EAT-26 total score BUT-GSI CBCL 6–18 subscale’s t-scores YSR 11–18 subscale’s t-scores MASC-2 subscale’s t-scores CDI-2 subscale’s t-scores
	Neuropsysiological	TEPs, SICI/ICF and SAI protocols MEP amplitude in iTBS protocol
	Physiological	CAR, CAR AUCg and AUCi Nutritional state and BMI

*APC* Affective problems, *BMI* Body Mass Index, *BUT* Body Uneasiness Test, *CBCL 6–18* Child behavior checklist for ages 6–18, *CDI-2* Children’s depression inventory—second edition, *AUCg* Cortisol area under the curve relative to the ground, *AUCi* Cortisol area under the curve with respect to the increase, *CAR* Cortisol awakening response, *EAT-26* Eating Attitudes Test, *EDI-3* Eating Disorder Inventory, *EDRC* Eating Disorder Risk, *GPMC* General Psychological Maladjustment, *GSI* global severity index, *IC* Ineffectiveness, *IPC* Interpersonal problems, *MEPs* Motor-Evoked Potentials, *MASC-2* Multidimensional Anxiety Scale For Children—second edition, *OC* Overcontrol, *SICI/ICF* Short intracortical inhibition and facilitation, *SAI* Short-latency afferent inhibition, *iTBS* Theta burst stimulation, *TEPs* TMS-evoked potentials, *YSR 11–18* Youth Self-Report for Ages 11–18.

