For secondary physiological outcomes, differences in saliva CAR, CAR AUCg and AUCi between groups (active tDCS + TAU vs sham tDCS + TAU) will be evaluated by repeated measures ANOVAs with time (T0 vs T1 vs T2 vs T4) as within-subject factors; and differences in BMI between groups (active tDCS + TAU vs sham tDCS + TAU) will be evaluated by repeated measures ANOVAs with time (T0 vs T1 vs T2 vs T3 vs T4 vs T5) as within-subject factors.

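### The BMI end-point is defined and analysed as raw kg/m² over more than a year in growing 10–18-year-olds; the active-versus-sham test stays unbiased, but within-arm change, the time effect and the correlation with clinical improvement include normal growth

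*Protocol article*

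**What the plan says.** All of the following is from the protocol article.

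- **Definition** (Physiological measures): "BMI will be calculated as the person’s weight in kilograms divided by the square of height in meters". No other form of the variable is given.
- **End-point** (Secondary outcome measures): "improvement in nutritional state and BMI, which have normative data for age and sex, will be adopted as secondary physiological end-points".
- **Analysis** (Statistical methods): "differences in BMI between groups (active tDCS + TAU vs sham tDCS + TAU) will be evaluated by repeated measures ANOVAs". All six assessments, T0 to T5, form the within-subject factor. No age or sex term is named.
- **Population** (Eligibility criteria): "age ranging from 10 to 18 years included".
- **Time span** (Participant timeline): six weeks of treatment to T1, with T5 one year later.
- **Use of BMI beyond the between-arm test** (Objectives): BMI is expected to improve after treatment, and changes in biomarkers, BMI among them, are to be correlated with clinical improvement.
- **Contrast with other outcomes** (Secondary outcome measures, Table 1, Statistical methods): the CBCL, YSR, MASC-2 and CDI-2 subscales are specified as t-scores.

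**The concern.** The article acknowledges that what counts as a normal BMI depends on age and sex, and then fixes and analyses a variable that ignores both. Over more than a year, a child whose weight stays at the same position relative to peers will usually gain raw BMI. The amount gained depends on age at entry. A rise in raw BMI is therefore a mixture of growth and weight recovery.

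Three uses of the end-point are affected:

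1. A statement that BMI improved after treatment, within an arm or through the time effect, would include growth.
2. The correlation of BMI change with clinical improvement would carry an age-related component. That component is noise if clinical response does not depend on age, and a confounder if it does.
3. A between-arm difference in kg/m², even if unbiased, has no single clinical meaning across this age range, because the same difference is a different shift relative to the norm at 10 and at 18.

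**Working it through.** **The plan's own figures.** None is given for BMI. The only sample-size figure concerns the EDRC score, and it reproduces. With f = 0.08, correlation 0.80, 2 groups, 6 measurements and sphericity assumed, the within-between interaction has λ = 0.08² × 68 × 6 / (1 − 0.80) = 13.06 on 5 and 330 degrees of freedom. Power is 0.8004 at N = 68, and 68 / 0.85 = 80. The scale of BMI has no bearing on this.

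**Inputs for the BMI check**

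- From the article: 40 per arm; age 10 to 18 inclusive; T0 to T5 = 6/52 + 1 = 1.115 years (58 weeks).
- Assumed, not in the documents: mean growth g of 0.3, 0.5 or 0.7 kg/m² per year; ages spread evenly over 10 to just under 19; growth rate falling linearly with age as 2g(19 − age)/9; SD of BMI change from all other causes 1.5 kg/m²; no treatment effect and no dropout.

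**Step 1: growth recorded as change.** Mean T0–T5 rise = g × 1.115:

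- 0.3 × 1.115 = 0.33 kg/m²
- 0.5 × 1.115 = 0.56 kg/m²
- 0.7 × 1.115 = 0.78 kg/m²

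Over treatment alone (T0–T1, 6/52 year) the range is 0.3 × 6/52 = 0.03 to 0.7 × 6/52 = 0.08 kg/m². The problem therefore lies mainly in the follow-up, not at T1.

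**Step 2: dependence on age.** At g = 0.5, entry at 10 gives 0.5 × 2 × 9/9 × 1.115 = 1.12 kg/m². Entry at 18 gives 0.5 × 2 × 1/9 × 1.115 = 0.12 kg/m².

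**Step 3: extra variance of change.** Growth is then uniform from 0 to 2g × 1.115, with SD = 2g × 1.115 / √12. The added variance relative to 1.5² = 2.25 is:

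- g = 0.3: SD 0.193; 0.037 / 2.25 = 1.7%
- g = 0.5: SD 0.322; 0.104 / 2.25 = 4.6%
- g = 0.7: SD 0.451; 0.203 / 2.25 = 9.0%

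**Step 4: what the tests do.** The T0–T5 change was simulated in 4,000 trials of 40 versus 40, with the same growth law in both arms. This reduces the six-level ANOVA to its longest contrast.

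| Assumed g (kg/m² per year) | Mean active − sham (kg/m²) | Rejection rate, group-by-change test | Rejection rate, time effect |
|---|---|---|---|
| 0.3 | 0.00 | 4.8% | 50% |
| 0.5 | 0.01 | 4.6% | 90% |
| 0.7 | 0.00 | 4.3% | 99% |

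The simulation error of a 5% rate is √(0.05 × 0.95 / 4000) = 0.34 percentage points, so the group test holds its level. The time effect is significant in half to nearly all trials although nobody's relative weight recovers.

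**The case against.** The strongest reply is that the quoted analysis compares randomised arms. Growth is expected equally in both, so it cancels in the group-by-time contrast, and the loss of precision is small. That stands, and the working confirms it. A reader might infer that the trial's BMI efficacy test counts growth as a treatment effect; the documents do not support that.

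A second reply is that standardisation may already be intended, since the article mentions norms where it adopts the end-point, and the BMI formula is the starting point for any z-score. Which reference to use could be left to a fuller document. This has some force. However, the article names the variable by formula, carries that name unchanged into the ANOVA, and says t-scores where it means standardised scores. As written, the analysis is of raw BMI.

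Three further inferences are tempting but do not hold:

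- *That allocation fails to balance degree of underweight.* The Allocation section takes age into account alongside BMI and EDI-3 severity, and it does not say on which scale BMI enters.
- *That the single cut-off, "a condition of under-weight (BMI < 18.5 kg/m^2"), contradicts the mention of norms.* It is an entry criterion that applies in addition to a clinically confirmed diagnosis, whereas the norms are mentioned for outcomes. The two statements can both stand.
- *That BMI is the leading physical outcome.* Table 1 lists it among the secondary physiological measures without rank.

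**Conclusion.** The point holds as a weakness in the scale and interpretation of a secondary end-point. It is not a bias in the randomised comparison. The primary outcome and the sample size are untouched.

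Raw BMI mixes growth with recovery in three places: within-arm change, the time effect, and the planned correlation with clinical improvement. It also leaves a between-arm difference in kg/m² without a uniform meaning over an age range for which the article itself says norms differ.

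On the assumed growth rates the spurious rise by T5 is about 0.33 to 0.78 kg/m², against 0.03 to 0.08 by T1. The variance of change grows by about 2% to 9%. These sizes rest on assumptions about growth and the SD of change that the documents do not supply. The direction of the problem rests only on the age range, the follow-up length and the stated formula. It should be corrected, because the remedy is cheap and better than the method stated.

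**What to change.** In Physiological measures, Secondary outcome measures and Statistical methods:

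1. Define the BMI end-point at T0 to T5 on one age- and sex-standardised scale, either a z-score or percent of median BMI, from one named reference. Make the choice before unblinding. Someone who enters during their nineteenth year of life reaches 19 or more by T5 (18 + 1.115 = 19.1), so state how the reference is applied above its upper age limit.
2. Use that variable in the repeated-measures ANOVA and in the correlation with clinical improvement. Report raw BMI descriptively.
3. State that conclusions about efficacy on BMI rest on the group-by-time contrast, not on change within an arm or on the time effect.

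The cost is one derived variable from weight, height, age and sex, with no new visits and no change in sample size. The drawback is that results then depend on the chosen reference, which is why it must be named in advance.

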### Participant timeline

Baseline assessment (at time 0-T0) will be completed before the interventions are administered. Participants will undertake tDCS treatments (active or sham) plus a TAU for six weeks delivered for three times a week (18 session). Participants will be evaluated at the end of the treatment (at time 1-T1) and one-month later (at time 2-T2), three months later (at time 3-T3), six months later (at time 4-T4) and one year later (at time 5-T5). In the last follow-up, participants will be asked to indicate whether they believe they were receiving active or sham tDCS.

See Fig. 1 for details on the specific assessment of each visit.

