### Sample size

The sample size was calculated by a priori analysis in G * Power, version 3.1.9.7 (The G*Power Team, Düsseldorf, Germany).

Assuming a correlation of 0.80 in the primary outcome measure (EDRC score of EDI-3 questionnaire) with an estimated f = 0.08, α value = 0.05 (i.e., probability of false positives of 5%), and β = 0.80 (i.e., at least 80% power), the sample size that was required for repeated-measures analysis of variance (ANOVA) with 2 groups (active tDCS vs sham tDCS) and 6 measurements (T0 vs. T1 vs. T2 vs. T3 vs. T4 vs. T5) was 68 (i.e., 34 per group). Considering a 15% dropout rate in the follow-ups, we will plan to recruit a total of 80 participants (i.e., 40 per group).

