### Statistical methods

The Shapiro–Wilk test will be used to test the normality of the data and Levene’s test for the homogeneity of variances. When data will be normally distributed and the assumption of homogeneity will be not violated, parametric analyses will be computed. When one assumption will be not meet, non-parametric tests will be conducted or a log-transformation of distribution will be applied, if appropriate.

The groups will be compared on demographic and categorical variables using Chi-Square analyses. The primary outcome (EDRC score of EDI-3) will be included in a General Linear Model and will be analyzed by means of repeated measures ANOVA with Group (active tDCS + TAU vs sham tDCS + TAU) as between-factor and Follow-ups (T0-T1 vs T0-T2 vs T0-T3 vs T0-T4 vs T0-T5) as within-factor. The same analyses will be applied to the secondary psychological outcomes (EAT-26 total score, BUT-GSI, and CBCL 6–18, YSR 11–18, MASC-2 and CDI-2 subscale’s t-scores). Post hoc comparisons will be run by means of Bonferroni test.

For secondary neurophysiological outcomes, the differences between the left and right hemisphere at baseline and between the recordings T0 and T1 will be evaluated on both TEPs component and frequency through a non-parametric cluster based permutation tests to correct for multiple comparisons as developed in the ft_timelockstatistics\ ft_freqstatistics functions in Fieldtrip [74]. The EEG signal will be analyzed for defining a resting state pattern with frequency inspection, using a Fourier analysis. For TMS data, prior to undergoing ANOVA, the normal distribution of data will be assessed by means of the Shapiro-Wilks test. The level of significance was set at 0.05. For the SICI, SAI, and iTBS protocols, we will perform three ANOVAs on the normalized values calculated as the percentage of the mean peak-to-peak amplitude size of the unconditioned TS with GROUP (active vs sham) as the between-subject factor and ISI (for SICI and SAI protocols) or TIME (for iTBS protocol) as within-subject factors. When a significant main effect will be reached, Bonferroni post hoc comparisons will be performed to characterize the specific effect.

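### BMI and cortisol outcomes: pre-treatment T0 is analysed as an outcome level and not as a covariate, and the deciding test is not named

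*Protocol article*

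**What the plan says.** The Secondary outcome measures section sets the physiological end-points as "reduction in the CAR, CAR AUCg and AUCi and improvement in nutritional state and BMI". The Participant timeline section places T0 before treatment: "Baseline assessment (at time 0-T0) will be completed before the interventions are administered".

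For the analysis, the last paragraph of Statistical methods says that "differences in BMI between groups (active tDCS + TAU vs sham tDCS + TAU) will be evaluated by repeated measures ANOVAs with time", the levels being "T0 vs T1 vs T2 vs T3 vs T4 vs T5) as within-subject factors". CAR, AUCg and AUCi are compared between groups in the same way, "with time (T0 vs T1 vs T2 vs T4) as within-subject factors". T0 is therefore one of six levels for BMI and one of four for the cortisol measures. No covariate is mentioned. The text does not say whether the group main effect or the Group x Time interaction answers the question, and the article names no interaction anywhere.

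The preceding paragraphs treat the primary and psychological outcomes differently. Their within-subject factor consists of changes from T0: "Follow-ups (T0-T1 vs T0-T2 vs T0-T3 vs T0-T4 vs T0-T5) as within-factor".

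**The concern.** The end-points ask whether BMI or cortisol moved differently after tDCS. Taken literally, a comparison between groups in this ANOVA is the group term, which compares the arms on the average of all visits. One of those visits precedes treatment and cannot show an effect, so a post-treatment difference is diluted. Stable differences between patients also stay in the error term, because the value that could remove them is used as an outcome.

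Group x Time does test differential change, but it spreads a sustained effect over 3 (cortisol) or 5 (BMI) degrees of freedom.

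The two terms have different nulls and can disagree. With neither named, a real effect could be missed, or the choice of term could be made after the results are seen.

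**Working it through.** **The plan's own figure.** The Sample size section gives f = 0.08, correlation 0.80, alpha 0.05, 2 groups, 6 measurements and N = 68, for EDRC.
- Interaction (or within-factor) formula: noncentrality f²·N·m/(1 − r) = 0.0064 × 68 × 6 / 0.20 = 13.06 on 5 and 330 df. Power is 0.800, so N = 68 is reproduced.
- Group main effect formula: f²·N·m/(1 + (m − 1)r) = 0.0064 × 68 × 6 / 5 = 0.52. Power is 0.11, and N = 1024 would be needed.

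The only power calculation in the article therefore matches an interaction or within-factor test. It concerns EDRC, not BMI or cortisol.

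**Inputs for BMI and CAR.**
- n = 34 per arm, which is the plan's N = 68.
- Two-sided 5%, outcome SD 1, compound symmetry, and a difference d = 0.4 SD at every visit after T0 (assumptions). For scale, f = 0.08 over six visits with a constant post-treatment difference implies 2 × 0.08/√(5/6 × 1/6) = 0.43 SD.
- Correlation r: none is given for these outcomes. The 0.80 is stated for the primary outcome only ("Assuming a correlation of 0.80 in the primary outcome measure (EDRC score of EDI-3 questionnaire"), so r = 0.5 and 0.8 are both shown.

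**Formulas**, with k levels including T0. The standard error of a group difference is √(2V/n).
- Group term: effect d(k − 1)/k, V = (1 + (k − 1)r)/k.
- Post-treatment mean, unadjusted: effect d, V = (1 + (k − 2)r)/(k − 1).
- T0-adjusted post-treatment mean: effect d, V = the previous line minus r².
- Group x Time: noncentrality λ = (n/2)·Σ(e − ē)²/(1 − r), on k − 1 and 66(k − 1) df, where e is the group difference at each visit.

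**Numbers in.** For BMI, d(k − 1)/k = 0.4 × 5/6 = 0.333 and Σ(e − ē)² = 0.16 × 5/6 = 0.133. For CAR they are 0.4 × 3/4 = 0.30 and 0.16 × 3/4 = 0.12.

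| Outcome, r | Group term | Post mean, unadjusted | Group x Time | T0-adjusted mean |
|---|---|---|---|---|
| BMI, 0.5 | V 0.583, 43% | V 0.600, 55% | λ 4.53, 32% | V 0.350, 78% |
| BMI, 0.8 | V 0.833, 32% | V 0.840, 43% | λ 11.33, 73% | V 0.200, 95% |
| CAR, 0.5 | V 0.625, 34% | V 0.667, 51% | λ 4.08, 36% | V 0.417, 71% |
| CAR, 0.8 | V 0.850, 26% | V 0.867, 42% | λ 10.20, 76% | V 0.227, 93% |

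**Where the loss arises.** Dropping T0 without adjusting for it moves the first column to the second. Adding the covariate moves the second to the last. For BMI at r = 0.8 these steps are 32 to 43 and 43 to 95 points; for CAR at r = 0.5 they are 34 to 51 and 51 to 71. In all four rows the larger step is the adjustment, narrowly so for CAR at r = 0.5. At r = 0.3 the order reverses.

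**Type I error.** A simulation of 4,000 trials gave null rejection of 5.2 to 5.7% for all three tests.

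**If the effect fades.** Take BMI differences of 0.60, 0.45, 0.30, 0.15 and 0 SD at T1 to T5 (an assumption). Group x Time has 68% power at r = 0.5 and 90% at r = 0.7; the T0-adjusted average has 54% and 65%. A T0-adjusted joint test over the five visits does not have this weakness. Its noncentrality is (n/2)/(1 − r) × [Σe² − (Σe)²·r/(1 + 5r)]. For Group x Time the last factor is 1/6 in place of r/(1 + 5r), and r/(1 + 5r) is below 1/6 for every r below 1. At r = 0.5, with Σe² = 0.675 and (Σe)² = 2.25, the values are 34 × (0.675 − 0.321) = 12.0 against 34 × (0.675 − 0.375) = 10.2.

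**The case against.** The strongest reply is that the article does not fix the group main effect as the test. In a two-arm pre/post ANOVA, Group x Time is the usual term for differential change. It needs T0 as a level, and the sample-size calculation matches it. **This stands.** A reader might infer that the plan tests the wrong hypothesis, but the text supports that only under one of two readings.

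A reader might also infer that the planned test loses most of its power, or that a real effect would probably be reported as no difference. Neither holds in general. For BMI at r = 0.5 the group term falls from 78% to 43%, less than half. At r = 0.8 Group x Time would detect a sustained 0.4 SD effect 73% of the time (76% for CAR). The article gives no correlation for these outcomes.

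Third, preferring an average over visits is a choice of estimand, and under a fading effect it loses to Group x Time (54% against 68% at r = 0.5). **This also stands**, against the average as the only remedy. It is no argument against adjusting for T0, since the adjusted joint test has the larger noncentrality.

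Fourth, the Allocation section already balances on BMI, so chance baseline imbalance is limited there. That worry applies mainly to the cortisol measures.

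Finally, an article may leave detail to a fuller document. Here, though, the article states the model and lists T0 as an outcome level, so this is a stated choice and not an omission.

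**Conclusion.** The point holds in a conditional form. For BMI, CAR, AUCg and AUCi, T0 is used as an outcome level and not as a covariate, and the deciding term is unnamed. If it is the group term, the hypothesis tested does not match the end-points and is inconsistent with the handling of the psychological outcomes. If it is Group x Time, the test is valid but less powerful than a T0-adjusted comparison when the effect is sustained.

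Against the T0-adjusted average, the group term is 35 to 67 percentage points lower and Group x Time 17 to 46 points lower across the four cases in the table. These sizes rest on 34 per arm, compound symmetry, a constant 0.4 SD effect and correlations of 0.5 to 0.8. Over that range the loss comes mainly from not adjusting for baseline, less from dilution by T0.

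False-positive risk is not raised. These are secondary outcomes, and the primary analysis is unaffected. The change is worth making but is not critical.

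**What to change.** In the last paragraph of Statistical methods:
- Take T0 out of the within-subject factor. Model only the post-treatment visits (T1, T2 and T4 for CAR, AUCg and AUCi; T1 to T5 for BMI), with each outcome's own T0 value as covariate.
- State in advance which T0-adjusted group contrast is the test: the average over visits if a sustained effect is expected, a named visit such as T1, or the joint test over visits if the effect may fade.
- Report visit-specific adjusted differences alongside.

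The cost is about two sentences of analysis wording. T0 is already collected for all four outcomes, so no visits, samples or participants are added.

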### Objectives

We hypothesized that excitatory tDCS over the left PFC and inhibitory tDCS over the right PFC (anode left/cathode right) may aid in altering/resetting inter-hemispheric balance in children and adolescents with AN, reducing their control over eating behaviors and improving the AN psychopathology, assessed as changes in Eating Disorder Risk composite score (EDRC) of the Eating Disorder Inventory (EDI-3) as primary outcome. The study also aims to investigate some neurophysiological mechanisms that characterize AN, as well as the association between efficacy and neurophysiological effect of tDCS treatment and physiological response to treatment, as secondary outcome. We will employ TMS-EEG to directly explore inter-hemispheric balance in the DLPFC activity of children and adolescent with AN. Moreover, paired pulse TMS (pp-TMS) and repetitive TMS (rTMS) protocols will be used to investigate the functional mechanisms within the PFC of youth patients with AN. We hypothesized that at baseline there are differences between the right and left hemisphere in some electrophysiological measures such as inhibitory/excitatory motor circuits, sensory-motor integration, cortical plasticity, cortical oscillations, reactivity, and functional connectivity, and that such differences will be reduced after tDCS treatment. In addition, an increase in cortical plasticity after tDCS treatment is expected. Finally, we will assess if potential changes of specific biomarkers, such as those related to the endogenous stress response system functioning, nutritional status and body mass index (BMI), will occur after tDCS treatment and correlate with clinical improvement. Specifically, we hypothesized a reduction of endogenous stress response and an improvement of nutritional status and BMI after tDCS treatment.

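### BMI is a secondary end-point linked to age and sex norms, but the plan defines and analyses only raw kg/m² over about 58 weeks at ages 10 to 18

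*Protocol article*

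**What the plan says.** Three sections of the protocol article bear on the BMI end-point.

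- **Secondary outcome measures** sets the end-point: "improvement in nutritional state and BMI, which have normative data for age and sex, will be adopted as secondary physiological end-points".
- **Physiological measures** gives the only definition: "BMI will be calculated as the person’s weight in kilograms divided by the square of height in meters".
- **Statistical methods** gives the analysis: "differences in BMI between groups (active tDCS + TAU vs sham tDCS + TAU) will be evaluated by repeated measures ANOVAs with time", with levels "T0 vs T1 vs T2 vs T3 vs T4 vs T5) as within-subject factors".

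None of these sections names an SDS, a percentile, a percent of median, a reference population, or an age or sex term in the model.

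Eligible ages are 10 to 18. The Participant timeline sets the treatment period ("tDCS treatments (active or sham) plus a TAU for six weeks delivered for three times a week (18 session") and places T5 one year after its end. The Objectives add that biomarker changes, BMI among them, are to be examined for whether they "will occur after tDCS treatment and correlate with clinical improvement". Allocation takes age, BMI and EDI-3 severity into account.

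**The concern.** Children and adolescents gain BMI as they grow. A patient whose position against the norms is unchanged at T5 can still have a higher raw BMI than at T0, and on the raw scale that reads as improvement. The same gain in kg/m² also stands for a different degree of weight recovery at 10 than at 18, so an arm mean of raw changes averages unlike quantities.

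The article points to norms in the end-point wording but does not carry them into the definition or the model. It does use age-normed scoring elsewhere: CBCL, YSR, MASC-2 and CDI-2 are analysed as t-scores. At stake is the meaning of any statement about weight recovery up to one year, and of any association between BMI change and clinical change.

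**Working it through.** **The plan's own figure.** No sample size or power is given for BMI. The stated size is for EDRC and reproduces. With f = 0.08, correlation 0.80, 2 groups and 6 measurements, λ = 0.08² × 68 × 6 / (1 − 0.80) = 13.06 on 5 and 330 degrees of freedom, which gives power 0.800. Then 68 / 0.85 = 80. Nothing below changes this.

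**Time span (from the Participant timeline).** T0 to T5 = 6 + 52 = 58 weeks, or 58/52 = 1.115 years. T0 to T1 = 6/52 = 0.115 years.

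**Growth alone (assumed).** The documents give no norms. Take a rise in healthy BMI of 0.3 to 0.8 kg/m² per year:

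| Interval | Low | High |
|---|---|---|
| T0–T1 | 0.3 × 0.115 = 0.03 | 0.8 × 0.115 = 0.09 |
| T0–T5 | 0.3 × 1.115 = 0.33 | 0.8 × 1.115 = 0.89 |

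Growth is negligible over treatment and potentially visible at one year.

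**Common scale (assumed medians 16.5 at the youngest age, 21 at the oldest).** A BMI of 16 is 16/16.5 = 97% of median in one patient and 16/21 = 76% in the other. A gain of 1 kg/m² against a fixed median is 1/16.5 = 6.1 percentage points in the first and 1/21 = 4.8 in the second.

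**Arm contrast.** The planned 2 × 6 ANOVA, with Greenhouse–Geisser correction, was simulated with growth and no treatment effect, 2,000 runs per setting. Assumptions:
- ages uniform from 10 to 18
- growth 0.3, 0.5 or 0.8 kg/m² per year, at 0.4 times that rate from age 16
- BMI SD 1.2 or 1.8
- within-person correlation 0.80, borrowed from EDRC
- N = 68 or 80, with 13.5 months from T0 to T5

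Group by time was rejected in 3.8% to 5.6% of runs, and the mean arm difference in T0–T5 change was within 0.01 kg/m² of zero. Growth does not bias the randomised comparison.

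**Time effect.** In the same runs the time main effect exceeded its nominal 5% in every growth setting. At N = 68 the frequency ran from 38% to 100%, depending only on the assumed growth rate and SD. This shows the direction and gives no usable estimate.

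**Noise in the arm contrast.** If individual growth varied uniformly from 0 to 0.8 kg/m² per year, its SD over T0–T5 would be (0.8/√12) × 1.115 = 0.231 × 1.115 = 0.258, variance 0.066.
- With an assumed SD of change of 2.0 or 1.5, that is 0.066/4.00 = 1.7% or 0.066/2.25 = 2.9% of the change variance.
- With the tightest simulation inputs, the change variance without growth is 2 × 0.20 × 1.2² = 0.576. Growth then adds 0.066/0.576 = 11.5%, which widens the standard error by √1.115 − 1, about 6%.

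**Correlation.** The Objectives give no time window. At T1 the growth component is at most 0.09 kg/m² under the assumptions above. At later visits it is larger and depends on age. It would confound the association only if clinical change also varied with age. Otherwise it adds noise and weakens the association.

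**The case against.** The strongest reply is that the planned analysis compares randomised arms. Growth cancels in expectation, and age and BMI are considered at allocation. In an add-on trial the pooled time effect also contains the effect of TAU, so it could not show tDCS efficacy on any scale. This stands. A reader might infer that normal growth would be counted as a treatment benefit, and the design does not support that.

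A reader might also infer that growth alone would make the T0–T5 change significant in a stated share of trials. That does not hold either. The article specifies no pairwise visit test for BMI, and the post hoc tests it plans for other outcomes are Bonferroni-corrected. Growth rate and SD are not in the documents, so any such percentage rests on assumptions.

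A third tempting reading is that the sections flatly contradict each other. Secondary outcome measures says that norms exist for BMI; it does not say that the end-point is a norm-referenced score. The formula in Physiological measures is also the first step towards any standardised score. The mismatch is therefore an unresolved ambiguity about which variable is analysed.

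The choice of reference could reasonably be left to a fuller document. What remains is that the article does fix a variable and a model, and as written the variable is raw.

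**Conclusion.** The point holds in limited form, as a minor one. The only BMI variable the article defines is raw kg/m², and that is what enters a T0–T5 analysis over about 58 weeks at ages 10 to 18, although the end-point wording refers to age and sex norms. The group-by-time contrast is unbiased and loses a little precision: a few percent of variance under most assumed inputs, about 12% at the tightest. Raw change is not comparable across ages. A time effect, a within-arm improvement or a long-term correlation with clinical improvement would be partly growth.

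How large that part is cannot be determined from the documents. The 0.33 to 0.89 kg/m² figure rests on an assumed healthy growth rate applied to patients whose growth may differ. BMI is one of many secondary end-points, and the primary outcome and the sample size of 68 (80 with dropout) are untouched.

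**What to change.** In Secondary outcome measures and Statistical methods, name the analysed variable as percent of median BMI for age and sex (or BMI SDS), with one named reference and exact age at each visit. Use the same variable when BMI change is correlated with clinical improvement. State that the conclusion about tDCS rests on group by time and not on the time effect alone. Keep raw BMI as a sensitivity result.

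The cost is one derived variable, built from weight, height, age and sex, and a few words of text. No new visits or measurements are needed. There are two small downsides: a reference must be chosen, and SDS can be less stable at very low weight, which percent of median avoids.
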